## Abstract

**Introduction:**

Within the UK, chest pain is one of the most common reasons for emergency (999) ambulance calls and the most common reason for emergency hospital admission. Diagnosing acute coronary syndromes (ACS) in a patient with chest pain in the prehospital setting by a paramedic is challenging. The Troponin-only Manchester Acute Coronary Syndromes (T-MACS) decision rule is a validated tool used in the emergency department (ED) to stratify patients with suspected ACS following a single blood test.

We are seeking to evaluate the diagnostic accuracy of the T-MACS decision aid algorithm to ‘rule out’ ACS when used in the prehospital environment with point-of-care troponin assays. If successful, this could allow paramedics to immediately rule out ACS for patients in the ‘very low risk’ group and avoid the need for transport to the ED, while also risk stratifying other patients using a single blood sample taken in the prehospital setting.

**Methods and analysis:**

We will recruit patients who call emergency (999) ambulance services where the responding paramedic suspects cardiac chest pain. The data required to apply T-MACS will be prospectively recorded by paramedics who are responding to each patient. Paramedics will be required to draw a venous blood sample at the time of arrival to the patient. Blood samples will later be tested in batches for cardiac troponin, using commercially available troponin assays. The primary outcome will be a diagnosis of acute myocardial infarction, established at the time of initial hospital admission. The secondary outcomes will include any major adverse cardiac events within 30 days of enrolment.

**Ethics and dissemination:**

The study obtained approval from the National Research Ethics Service (reference: 18/ES/0101) and the Health Research Authority. We will publish our findings in a high impact general medical journal.

**Trial registration number:**

Registration number: ClinicalTrials.gov, study ID: NCT03561051

Strengths and limitations of this studyPrehospital Evaluation of Sensitive Troponin is a multicentre prospective observational diagnostic accuracy study recruiting patients from four ambulance services in the UK, so we anticipate that our result truly reflects UK practice.The future clinical use of Troponin-only Manchester Acute Coronary Syndromes in the prehospital setting will be limited due to the observational study design pending a definitive randomised controlled trial.The study captures a large amount of data which allow the study team to evaluate different emergency department strategies used to risk stratify patients with chest pain in the prehospital setting.The study evaluates three different point-of-care troponin assays in conjunction with multiple validated decision aids.

## Introduction

Chest pain is one of the most common reason for emergency hospital admission. Clinicians will suspect a diagnosis of acute coronary syndromes (ACS) in approximately half of the patients presenting to emergency departments (EDs) with chest pain, accounting for the majority of these admissions. However, less than 20% of those admitted to hospital on the suspicion of ACS actually have that diagnosis. Most of these admissions could be avoided with improved diagnostic technology.^1–3^

In recent years, there has been much work performed in the ED setting with the aim of rapidly risk-stratifying patients with cardiac chest pain with a view to early discharge of those who are at low risk. The Troponin-only Manchester Acute Coronary Syndromes (T-MACS) is a scientifically derived mathematical model that combines clinical and historical features with ECG and cardiac biomarker results to determine the probability of ACS and assign patients to one of four risk groups: very low risk (<2% probability), low risk (2%–5% probability), moderate risk (5%–95% probability) and high risk (probability ≥95%).

T-MACS has been shown to effectively reduce unnecessary hospital admissions when used in the ED.^4^ It identifies 45% of patients as eligible for safe, immediate discharge following a single blood test.^4 5^ This is demonstrably superior to other early rule-out strategies, including that recommended by National Institute for Health and Care Excellence (NICE) prior to publication of our findings. In addition to ‘ruling out’ a diagnosis of ACS and reducing the need for unnecessary investigations and hospital admission, T-MACS can also ‘rule in’ the diagnosis in approximately 5% of patients with 95% positive predictive value, facilitating early specialist treatment.^4–7^

The original T-MACS model relies on laboratory-based troponin testing. In the multicentre Bedside Evaluation of Sensitive Troponin (BEST) study, we have evaluated the accuracy of T-MACS with point-of-care (POC) troponin assays that use portable/handheld analysers, which could be used in ambulances. Results from the BEST study demonstrate that, with a contemporary POC test, T-MACS ‘ruled out’ ACS in 42.7% of patients with 95.5% sensitivity and 98.7% negative predictive value.^5^

Using portable POC tests, T-MACS could remove the requirement for many patients with suspected ACS to be assessed in the hospital, enabling even earlier reassurance for patients and cost savings for the National Health Service (NHS). Given the high prevalence of chest pain, avoiding ED attendances will reduce crowding, which leads to more patient safety incidents and higher mortality. Similarly, avoiding unnecessary transfer to hospital will free up ambulances to answer other emergency calls. However, as blood tests will be taken sooner after symptom onset, it is not safe to assume that T-MACS will be accurate in the prehospital environment. We must formally evaluate its accuracy in that setting.

### Aims and objectives

The primary objective of Pre-hospital Evaluation of Sensitive Troponin is to evaluate whether paramedics can use troponin testing by a handheld device with a computerised algorithm at the time of arrival to patients with symptoms that cause the treating paramedic to suspect the diagnosis of ACS. This would avoid unnecessary transfer and enable accurate identification of: (1) patients who do not have acute myocardial infarction (AMI) and therefore do not need to be taken to hospital; and (2) patients who do have AMI and therefore need to be given early treatment in the prehospital environment for their condition. Secondary objectives include validating the T-MACS decision aid that could be used to enhance the early diagnosis of AMI.

## Methods and analysis

### Design and setting

We will undertake a multicentre, prospective diagnostic accuracy study involving ambulance services and EDs in the UK. We started participants recruitment on February 2019 and we will complete recruitment within 12 months.

Within each ambulance service, research activity will be focused at ambulance stations or hubs with (1) a track record for successful delivery of similar research; and (2) which feed into hospitals with (a) adequate central laboratory support for sample processing and storage, and (b) clinical protocols that adhere to national and international standards for the investigation of patients with suspected ACS.

### Data collection

#### Prehospital environment

Paramedics will record basic clinical data using a brief case report form at the time of inclusion. The data collected will be sufficient to enable calculation of the T-MACS decision aid outcome, including the treating paramedic’s interpretation of the patient’s 12-lead ECG. However, in this observational study, the T-MACS rule outcome will not be known to paramedics.

Paramedics will receive bespoke study training before signing the signature log. After participating paramedics have provided any necessary urgent treatment and obtained verbal consent, they will undertake venepuncture prior to transferring the patient. If paramedics are inserting an intravenous cannula, blood will be drawn at the same time. Less than 5 mL venous blood will be drawn and stored in a lithium heparin bottle labelled with a unique study identifier. The date and time of venepuncture will be logged on the case report form and on the blood bottle. All patients will then be transferred to hospital in accordance with routine care.

#### Hospital environment

On arrival at the hospital, all patients will undergo reference standard troponin testing in accordance with contemporary national and international guidance. Acceptable protocols for reference standard troponin testing include:

If a contemporary (not high sensitivity) troponin assay is used: laboratory-based troponin testing on arrival and either 6 hours after arrival, or 10–12 hours after the onset of peak symptoms.If a high sensitivity troponin assay is used: laboratory-based troponin testing on arrival and either 3 hours after arrival, or 6 hours after the onset of peak symptoms, unless the patient has undergone investigation according to a validated rule-out protocol as advocated in national international guidelines.

A high-sensitivity troponin assay is defined as an assay that can detect troponin concentrations in at least 50% of apparently healthy individuals with a co-efficient of variation of <10% at the 99th percentile cut-off.

When the patient arrives at the ED, the local study team will be informed. A member of the study team will either send the lithium heparin sample drawn in the prehospital environment up to the central laboratory for processing and storage, or the sample will be processed and stored by a member of the study team who has had appropriate training. Once the patient has received all initial treatment in accordance with routine care, a member of the local research team will then approach them to answer any questions they may have about the study and obtain written informed consent.

If the research team cannot obtain written informed consent at the time of participant admission to the ED, the research paramedic will follow this up and obtain written informed consent via post, electronically or over the phone. The research paramedic will have 4 weeks to obtain written informed consent before the participant is withdrawn from the study and their samples destroyed. The participant will be made aware of this deadline in the information that is sent to them before they are approached for consent. If the participant is followed up via postal consent, a 1-week grace period will be given to allow for delays in the postal service. After this, the participant will be withdrawn from the study and their study data and samples will be destroyed.

One hour (±30 min) after the prehospital blood has been taken; a member of the research team will draw another sample of venous blood (<5 mL) into the provided lithium heparin bottle labelled with the participant’s unique study identifier. The date and time the blood was drawn will be logged on the case report form and on the blood bottle. This venous blood sample will be sent up to the central labs for processing and storage or will be processed and stored by the local research team.

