### Outcomes

The primary outcome will be a diagnosis of AMI, established at the time of initial hospital admission. To diagnose AMI according to internationally accepted standards requires serial troponin sampling. This will help to ensure adequate reference standards for the diagnosis of AMI. Outcomes will be adjudicated by two independent investigators with reference to relevant clinical information but blinded to the results of research investigations. Discrepancies will be resolved by a third independent investigator. AMI will be defined according to the Fourth Universal Definition.^11^ By virtue of the inclusion criteria, all patients will have symptoms and signs consistent with myocardial ischaemia. Briefly, therefore, patients will be deemed to have met this outcome if they develop a rise and/or fall of troponin to above the 99th percentile.

The secondary outcomes will include any major adverse cardiac events, which include cardiovascular death, coronary revascularisation and incident AMI within 30 days. All causes of death occurring within 30 days and the final diagnoses of all patients will also be recorded.

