#### Secondary analyses

We are planning to conduct several secondary analyses. First, we will evaluate the diagnostic accuracy of T-MACS as a ‘rule-in’ tool, which would facilitate direct transfer to tertiary care heart attack centres and may enable patients to benefit from earlier specialist treatment such as percutaneous coronary intervention in future. To do this, we will dichotomise T-MACS at the probability threshold of 95% (ie, analysing classification as ‘high risk’ vs all other risk groups). We will again calculate sensitivity, specificity, positive and negative predictive values, positive and negative likelihood ratios and their respective 95% CIs. Finally, we will calculate the proportion of patients with and without ACS who would have been transported to tertiary care facilities if T-MACS had been used in practice, and we will compare those findings to the observed practice in routine care. As some patients may have final diagnoses other than ACS, we will also retrieve the final coded diagnosis for all patients and present a descriptive analysis stratified by T-MACS risk group.

Second, we will evaluate the diagnostic accuracy of other hospital-based strategies used to rule-out, rule-in or ‘risk-stratify’ patients with AMI or ACS such as the HEART (History, ECG, Age, Risk factors, Troponin) score, History and ECG only Manchester Acute Coronary Syndromes (HE-MACS) decision aid, limit of detection strategy and selected cut-offs (eg, the 99th percentile of a reference population).

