## Discussion

Based on our experience with previous studies, if our findings are positive we will aim to achieve clinical implementation within 2 years. Clearly, this will involve additional work to demonstrate the feasibility and acceptability of ‘live application’ of T-MACS in the ambulance; to develop new clinical guidelines and training regimes and to robustly communicate the clinical and cost effectiveness of the strategy.

The recent update to NICE Guideline CG95 incorporated a novel diagnostic strategy (originally developed by our group) for in-hospital use based on data from observational studies with a similar design. Given that precedent, we anticipate that our findings will generate the evidence required by NICE to issue a recommendation for the clinical use of T-MACS with a POC troponin assay in the prehospital environment.

We also implemented T-MACS in the hospital environment primarily based on observational data. The algorithm has been applied in 8000 patients and has led to 2/3 patients being safely treated in an ambulatory care environment without requiring hospital admission. Health Innovation Manchester, with access to a Joint Commissioning Board, has adopted T-MACS as an exemplar project for rapid implementation across Greater Manchester. We will conduct a ‘phase 4 evaluation’ of that regional implementation, aiming to achieve more widespread clinical implementation within 24 months of completion. If the findings of the proposed study are positive, we will use a similar methodology to achieve rapid implementation in the prehospital environment.

If successfully implemented in practice, we anticipate that our findings will avoid the need for unnecessary ambulance transfers and hospital admission in approximately 40% of patients. As chest pain is the second most common reason for emergency ambulance calls and most common reason for emergency hospital admission, this is likely to have a substantial economic impact while reducing hospital overcrowding and its associated complications.

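### At high-sensitivity sites the reference standard can omit the timed second troponin, so an AMI missed by a hospital rule-out pathway would count as a primary-outcome negative

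*Protocol article*

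**What the plan says.** The Hospital environment section gives two acceptable reference protocols.

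- **Contemporary assay:** "laboratory-based troponin testing on arrival and either 6 hours after arrival, or 10–12 hours after the onset of peak symptoms", with no exception.
- **High-sensitivity assay:** a sample on arrival and a timed second sample, "unless the patient has undergone investigation according to a validated rule-out protocol as advocated in national international guidelines". The text does not say how many samples such a protocol must contain.

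The Outcomes section states: "To diagnose AMI according to internationally accepted standards requires serial troponin sampling". A patient meets the primary outcome "if they develop a rise and/or fall of troponin to above the 99th percentile". On timing: "The primary outcome will be a diagnosis of AMI, established at the time of initial hospital admission". Two adjudicators, with a third for disagreements, see the clinical information but not the research results. Events up to 30 days, including "coronary revascularisation and incident AMI within 30 days", belong to the secondary outcome.

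Three other places bear on this. The Introduction describes T-MACS as allowing discharge after one blood test. The Discussion says: "We also implemented T-MACS in the hospital environment primarily based on observational data". It adds that a strategy from the same group is in the national guideline, without naming it. The Secondary analyses evaluate the HE-MACS "decision aid, limit of detection strategy and selected cut-offs" alongside T-MACS.

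**The concern.** A single troponin value cannot show a rise or a fall. If an accepted rule-out protocol rests on one sample, a patient cleared by it has no troponin route to a positive primary outcome. Even where the protocol has two early samples, the patient has had less verification than one sampled at the stated interval.

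The patients affected are those judged low risk in hospital, and T-MACS false negatives are most likely to be found among them. A hospital pathway and prehospital T-MACS may share inputs (history, ECG, troponin), so they may miss the same patients. Each such shared miss moves from false negative to true negative in the primary table. The resulting sensitivity and NPV are what the Primary analysis and Discussion would use to support leaving very-low-risk patients at home, so a few misclassified patients matter.

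**Working it through.** **1. The protocol's own figure.** Sample size gives N = 605, prevalence 10%, specificity 45%, and lower 95% limits above 90% (sensitivity) and above 99% (NPV) if both are observed at 100%.

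- AMIs: 605 × 0.10 = 60.5, taken as 60. The exact lower limit at 60/60 is 0.025^(1/60) = 94.0%, so the sensitivity statement reproduces.
- True negatives: 605 × 0.90 × 0.45 = 245. The exact lower limit at 245/245 is 0.025^(1/245) = 98.5%, so the NPV statement does not reproduce. That is a separate matter. Only the 90% mark for sensitivity is used below.

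**2. Direction.** Let TP and FN be the true T-MACS counts among AMIs. Let h be the T-MACS-negative AMIs, and b the T-MACS-flagged AMIs, that the hospital pathway hides.

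- Apparent NPV = (TN + h)/(TN + FN). It rises with h and does not depend on b, so its bias is upward or zero.
- Apparent sensitivity = (TP − b)/(TP − b + FN − h). It exceeds the true value only if h/(h + b) > FN/(TP + FN), that is, if hidden AMIs are T-MACS-negative more often than AMIs overall.

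**3. Illustration.** The documents give neither the share of waived patients nor the AMIs missed among them, so both are assumed. With 60 AMIs and the 95.5% sensitivity quoted in the Introduction, 60 × 0.045 = 2.7, taken as 3 false negatives. Limits are exact two-sided 95% lower limits.

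| Hidden: T-MACS-negative / T-MACS-flagged | Sensitivity | Lower limit | NPV | Lower limit |
|---|---|---|---|---|
| 0 / 0 (truth) | 57/60 = 95.0% | 86.1% | 245/248 = 98.8% | 96.5% |
| 1 / 0 | 57/59 = 96.6% | 88.3% | 246/248 = 99.2% | 97.1% |
| 2 / 0 | 57/58 = 98.3% | 90.8% | 247/248 = 99.6% | 97.8% |
| 3 / 0 | 57/57 = 100% | 93.7% | 248/248 = 100% | 98.5% |
| 1 / 1 | 56/58 = 96.6% | 88.1% | 246/248 = 99.2% | 97.1% |
| 0 / 2 | 55/58 = 94.8% | 85.6% | 245/248 = 98.8% | 96.5% |

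Here sensitivity is inflated once more than 3/60 = 5% of hidden AMIs are T-MACS-negative. The last row is the exception: if both hidden AMIs were flagged by T-MACS, sensitivity falls slightly.

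**4. Dependence on the assumed false negatives.** With 1, the true lower limit is already 91.1%. With 2 (true limit 88.5%), hiding 1 gives 90.9%. With 4 (true limit 83.8%), hiding 3 gives 90.6%. With 6 (true limit 79.5%), hiding 3 gives only 85.4%.

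**5. What a serial-troponin-only analysis can do.** Patients ruled out on one sample are never reference-positive. Dropping them leaves TP and FN, and so sensitivity, unchanged. Only the true-negative and false-positive counts move, so it can inform NPV and specificity but cannot recover a hidden AMI.

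**The case against.** The strongest reply has five parts.

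- **Scope.** The exception covers only the high-sensitivity branch and only guideline-advocated, validated protocols. This stands and limits how many patients are affected.
- **Number of samples.** Accepted protocols may be short serial ones, which can show a rise or fall. This stands too: single-sample use is an inference. The text permits it but does not state it.
- **Softness of the conflict.** Serial sampling is said to be needed to diagnose AMI, while the exception concerns ruling it out. That softens the conflict but does not remove it, because a diagnostic accuracy study needs the reference standard to establish absence as well as presence.
- **Safeguards.** Dual adjudication uses the full clinical record, and 30-day events are collected. Adjudicators cannot see a change in a single value, however. They are also blinded to the one-hour research sample, which is planned for point-of-care assays. The 30-day events are a real partial check, but they feed only the secondary outcome.
- **Independence of the tests.** A reader might infer that the reference standard can be the index test itself. The documents do not support that. The index test uses prehospital blood, point-of-care assays and the paramedic's ECG reading, whereas the hospital pathway would use a later sample and a high-sensitivity laboratory assay. Nor do they say that T-MACS is guideline-advocated, and the roll-out they describe is regional. What remains is the possibility of correlated error.

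**Conclusion.** The two sections disagree on what an adequate reference standard is, and the disagreement reaches the primary outcome. An AMI missed on a waived pathway is counted as a negative. NPV is then biased upward or not at all. Sensitivity is likely inflated, provided that hospital misses and T-MACS misses coincide more often than T-MACS misses AMIs overall. Shared inputs make this plausible but do not prove it.

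The size is unknown, and at sites where no one is waived it is zero. In the illustration, two concordant misses among 605 patients carry the lower limit for sensitivity from 86.1% to 90.8%. That result assumes 60 AMIs, 3 true false negatives and no recovery by adjudicators. The 90% mark is the protocol's precision target under perfect observed sensitivity. It is not stated as a formal decision rule.

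A reader might also infer a definite size from the earlier emergency department study: 605 × 0.427 = 258 patients cleared, 258 × 0.013 = 3.4 missed AMIs, and true sensitivity of 60/63.4 = 94.7% behind an observed 100%. The documents do not support this as an estimate. Those inputs are for T-MACS with a contemporary point-of-care assay and are reported for ACS, while the exception concerns high-sensitivity laboratory assays. The calculation also supposes that every eligible patient is waived and every miss is shared. It is a worst case.

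**What to change.** - **Reconcile the two sections.** Hospital environment and Outcomes should agree on whether a patient investigated under the exception has an adequate reference standard for the primary outcome. This concerns classification in the study and leaves hospital testing as it is.
- **Record the reference pathway.** For each patient, note the assay type, the number and timing of laboratory troponins, and whether the exception applied and under which protocol. Report waived patients by T-MACS risk group.
- **Keep the stated primary outcome and prespecify a sensitivity analysis.** Recompute sensitivity, specificity, predictive values and likelihood ratios with waived patients classified by index-admission data plus adjudicated 30-day AMI or cardiovascular death. Fix this before T-MACS results are linked to outcomes.
- **Optional:** an analysis restricted to patients with serial troponins, presented for NPV and specificity only.

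**Cost.** The changes are wording, one recorded item and one added analysis. No extra blood draw is needed, and the inpatient and 30-day data are already planned, so it remains feasible although recruitment has begun. The downside is small. Reference status for waived patients would rest on follow-up, a 30-day AMI may be new rather than missed, and a missed AMI without a later event stays negative. Waived patients without 30-day follow-up should be counted separately.
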